#### **i) Blood samples for biomarkers**

Samples must only be taken after provision of separate consent for genetic sampling and ideally prior to administration of investigational product. Blood samples taken at discontinuation should have a record of the time passed since last dose of trial treatment. See [section 21](#) for details of samples.

#### **j) Post-mortem samples**

Post-mortem tumour samples should be arranged if the patient has discontinued due to death, and the deceased patient has given explicit consent for this. See [section 21](#).

### k) Assessment dates during trial treatment

The cycle start assessment should be carried out on the day the patient begins the next cycle of study treatment. **Clinic assessments and MRI assessments will occur at the specified time points irrespective of trial treatment holidays.** E.g a 6 week cycle may only contain 3 or 4 weeks of trial treatment if a patient has had a trial treatment holiday during that cycle. If either treatment is delayed for more than 14 days due to toxicity (or 21 days if the CI has permitted a 21 day treatment holiday), the patient should cease taking the medication and continue with the cycles of the other study treatment. If both the study treatments are delayed for more than 14 days due to toxicity (or 21 days if the CI has permitted a 21 day treatment holiday), the discontinuation assessment should be performed and the patient withdrawn from the trial.

### l) Time between screening and baseline

A maximum of 14 days between screening and baseline is permitted. However for patients switching from enzyme inducing anti-epileptic drugs to non-enzyme inducing anti-epileptic drugs, this can be extended to a maximum of 21 days before baseline (as a wash-out period of 2 weeks is required. See 5.1.2 Exclusion criteria). Screening assessments must be performed within 7 days before randomisation, as per [section 5.2](#) (pre-randomisation evaluation). **If more than 14 days pass between screening and baseline, the randomisation form must be updated with pre-randomisation tests completed within 14 days of the baseline visit and this reassessed for eligibility at UCL CTC before the patient proceeds with the baseline assessments.**

### m) Concomitant medication collection after discontinuation

After discontinuation – concomitant medication for treatment of brain tumour only should be collected (e.g radiotherapy, chemotherapy, investigational drugs).

## 8.3 Patient diaries

Patients will be provided with a diary and encouraged to record daily blood pressure readings, compliance in taking study medication, and dexamethasone dose taken. These will be read by the site staff at assessment visits to assist with completing the CRFs. Patient diaries should be completed until progression is documented and returned to the site staff at each clinic visit.

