Change in signal intensity in T2/FLAIR within the original enhancing volume would not be sufficient for evidence of tumour progression.

The date of progression will be determined as being the date of the first MRI scan fitting the criteria for progression, or the date the clinical deterioration or death was first reported, whichever is earliest.

Locally reported progression should be determined by the above criteria. However, due to the possibility of pseudoprogression in these patients, a confirmatory second scan taken 6 weeks after the first should be used when making treatment decisions based on radiological progression. Please note it is not necessary to stop the trial drug in patients who have progressed only radiologically (even if confirmed at subsequent visits) if the clinician feels that the patient is benefiting from treatment.

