#### **7.4.1.4 Hypertension management**

Patients will be provided with blood pressure monitors at the beginning of the trial to monitor blood pressure at home on a daily basis and will be encouraged to record this in the patient diaries. Data from the diaries will be used by the site staff to complete the CRFs at each assessment.

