| Severe hypertension:

Increase in diastolic pressure to $\geq 110$ mmHg or increase in systolic pressure to $\geq 180$ mmHg on 2 readings >1 hour apart | 
 
1. Temporarily stop cediranib and consider if hospitalisation is necessary.
 
2. Initiate treatment with a 2-drug combination including a calcium channel blocker licensed for use in severe hypertension, tailored to the patient's underlying conditions and previous anti-hypertension treatment.
 
3. If there is evidence of target-organ damage, intravenous therapy should be considered while continuing oral therapy.
 
4. Nitrates may adversely affect the therapeutic mechanism of action of cediranib but should be used if clinically indicated.
 
5. Restart cediranib at 1 dose lower than the starting dose when BP <140/90 mmHg. Monitor BP every 3 to 7 days until steady state is BP stabilised
 
6. If BP increases to >160/95 mmHg, temporarily stop cediranib and continue anti-hypertensive therapy under close supervision.
 
7. Restart cediranib at 2 doses lower than the starting dose when BP <140/90 mmHg. Monitor BP every week until steady state is BP stabilised.
 
8. If BP increases to >160/95 mmHg after dose reduction to 15 mg od, despite anti-hypertensive therapy, permanently stop cediranib.
 
 |

The development of hypertension in patients treated with cediranib is generally an early event, usually occurring in the first 4 weeks of treatment. In a minority of patients hypertension can also occur later in a treatment schedule.

The rigorous monitoring of BP and adherence to the hypertension management guidelines are necessary in order to achieve optimal hypertension control. Patients on prior anti-hypertension therapy may be particularly at risk of developing moderate or severe hypertension on cediranib. Therefore, patients with pre-existing hypertension or on anti-hypertension medications are likely to benefit from having their BP management optimised before starting cediranib.

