For all BP thresholds described in this protocol, a trigger level is considered to be met if either the systolic and/or diastolic pressure reaches the threshold. If the threshold is recorded at home, it must be confirmed by a healthcare professional as defined above before commencing any treatment. CLEAR reasons for progressing to the next step in the management protocol must be documented. When managing mild to moderate hypertension, the following principles should be noted:

- Cediranib may cause rapid increases in BP in some patients
- Calcium-channel antagonists are the first line agents of choice
- Increase anti-hypertensives to maximum doses and add additional agents as required.
- It is recommended that no more than 2 drugs are added in a 48-hour period before temporarily stopping cediranib.

The following cautions and contraindications should be noted:

- Calcium-channel blockers: use with caution in patients with tachyarrhythmias, aortic stenosis, unstable angina or congestive cardiac failure and may cause headache
- Short-acting non-dihydropyridines such as diltiazem or verapamil should be avoided since they may precipitate abrupt fall in BP and increase risk of myocardial ischaemia, infarction or stroke
- Beta-blockers: contraindicated in patients with asthma, chronic obstructive pulmonary disease and A-V block; they should be used with caution in patients with peripheral vascular disease and glucose intolerance and may cause fatigue
- If diuretics are to be used, thiazides rather than loop diuretics are recommended

A record of the management of hypertension will be maintained.

CTCAE grade 3 should NOT be assigned to hypertension AEs on the basis of the number of drugs used according to this protocol to treat mild-moderate hypertension since this is a proactive treatment approach. CTCAE grade 3 should be assigned **if hypertension is not controlled after 7 days of per-protocol anti-hypertensive therapy.**

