## 8.2 Schedule of Assessments – further details

### a) Physical Examination

Including height, weight, lying and 5 minute standing blood pressure, ECOG performance status. Patient's blood pressure needs to be monitored weekly for the first 6 weeks of treatment of cediranib +/- gefitinib. Patients/carers will monitor the patient's blood pressure daily and record this in the patient diaries. CRFs should reflect an average of the patient-reported daily values. If a patient has BP  $\geq 150/100$  mmHg at Screening, a further reading should be taken at least 24 hours later to assess eligibility. In event of hypertension, refer to hypertension management plan, see [Section 7.4.1.4](#).

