#### **h) Follow up assessment schedule after discontinuation**

If a patient discontinues due to reasons other than progression, the patient will continue to be followed-up every 6 weeks until progression or death. If a patient discontinues due to progression, or has progressed after discontinuation, the patient will continue to be followed-up every 12 weeks for survival (via telephone call). All efforts should be made by the Site to contact the patient's GP to assess their condition, if a patient fails to attend a clinic or cannot be followed up at site. The trial will be registered with the NHS Information Centre in the event that any patients become Lost to Follow Up.

Neurological status assessments should be continued until neurological deterioration has been documented on 2 consecutive 6 weekly assessments. Dexamethasone dose per day should be collected until progression documented (as outlined in [section 2.6.1.1](#))

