If disease progression has been documented and the patient has withdrawn from study treatment, the long-term follow up information should be collected at least every 12 weeks by telephone contact with the patient, patient's family, or by contact with the patient's physician (see [section 8](#)). Please note that withdrawal from trial treatment is not compulsory for patients with disease progression, if the investigator feels that the patient is receiving benefit from trial treatment.

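### The diary stops at progression, but trial treatment need not, so the written home blood pressure record can end while patients still take cediranib

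*Protocol*

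**What the plan says.** Protocol section 8.3 describes a single diary for daily BP, study-drug intake and dexamethasone dose, which site staff read at visits to help complete the CRFs. All three items share one stopping rule: "Patient diaries should be completed until progression is documented".

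Treatment has a different end-point. Section 2.6.1.1 says "it is not necessary to stop the trial drug in patients who have progressed only radiologically" if the clinician believes the patient is benefiting. Section 13.1.2 is broader: "Please note that withdrawal from trial treatment is not compulsory for patients with disease progression", again subject to the investigator's view of benefit. Sections 7.1, 7.2 and 13.1 agree, and the schedule in section 8.1 runs the on-treatment visits until discontinuation.

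Other sections use the diary without a progression limit. On BP, section 7.4.1.4 states "Data from the diaries will be used by the site staff to complete the CRFs at each assessment", and section 8.2 a adds "CRFs should reflect an average of the patient-reported daily values". Section 7.3.1 encourages patients to note study-drug intake each day. The exception is dexamethasone, for which section 8.2 h says "Dexamethasone dose per day should be collected until progression documented".

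**The concern.** The 8.3 stopping rule suits one of the three diary items. Dexamethasone is needed only up to progression, because the steroid endpoints in section 16.4 stop there. BP and study-drug intake are on-treatment records, and treatment can outlast progression. Applied as written, 8.3 ends the day-by-day written record of both while the patient is still taking cediranib, a drug for which the protocol provides a detailed hypertension plan.

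Two things are at stake:

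- **Data.** The CRF item for average patient-reported BP loses its written source in these patients, although vital signs including BP are a listed safety outcome (sections 2.6.3 and 16.5).
- **Monitoring.** A home reading is one way into the hypertension plan; section 7.4.1.4 says "If the threshold is recorded at home, it must be confirmed by a healthcare professional" before treatment starts. The diary is where staff read those values. The same section warns that "In a minority of patients hypertension can also occur later in a treatment schedule", so onset after progression is possible and could be picked up later or less completely.

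**Working it through.** The protocol gives no figure to reproduce. The check is a comparison of sections plus one interval calculation.

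**Step 1: end-points side by side**

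| Diary item | Where its use is set | End-point there | End-point under 8.3 | Consistent? |
|---|---|---|---|---|
| Home BP | 7.4.1.4, 8.2 a | None given; visits run to discontinuation (8.1) | Documented progression | No, if treated past progression |
| Study-drug intake | 7.3.1 | None given; relevant while on drug | Documented progression | No, if treated past progression |
| Dexamethasone | 8.2 h, 16.4 | Progression | Documented progression | Yes |

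**Step 2: who is affected.** Anyone kept on trial drug after progression is affected. Sections 2.6.1.1 and 13.1 also ask for a confirmatory scan 6 weeks later before a treatment decision or withdrawal based on radiological progression alone. Section 8.3 does not say whether progression counts as documented at the first qualifying scan or only once confirmed. On the first reading, a patient with radiological progression only would stop the diary about 6 weeks before the scan meant to settle whether to stop treatment. On the second, the gap is confined to patients kept on treatment after confirmation. The protocol gives no number for either group.

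**Step 3: scheduled BP that remains.** BP is part of the physical examination (8.2 a). The 8.1 schedule has that examination weekly from week 1 to week 6, then at cycle-start visits every 6 weeks and at discontinuation. There is none at the mid-cycle visits. Visit windows are ±3 days.

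- Nominal gap between clinic readings: 6 × 7 = 42 days.
- Longest gap within the windows: 42 + 3 + 3 = 48 days.

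**Step 4: the comparator with a diary.** Visits alternate between mid-cycle and cycle start every 3 weeks, and staff read the diary at each.

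- Nominal interval between diary reviews: 3 × 7 = 21 days.
- Longest interval within the windows: 21 + 3 + 3 = 27 days, with up to one reading per day in between.

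For a patient with no known hypertension, ending the diary moves the scheduled written BP information from daily values reviewed about every 21 days to a single clinic value about every 42 days.

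**The case against.** The best defence is that this is a loose end and not a true contradiction. Sections 7.4.1.4 and 8.2 a set no duration, 8.3 does, and the texts can be read together; 8.3 does not forbid later entries. Diary entries are mostly only encouraged (7.3.1, 7.4.1.4, 8.3), so little that is mandatory is lost. Home measurement is not stopped, so the 42 to 48 days between clinic readings is not a detection delay. Hypertension usually appears in the first 4 weeks, and the first scheduled on-treatment scan is at week 6, by which time weekly clinic BP has been done. Patients already hypertensive follow Table 7, which has its own checks and no progression cut-off. Drug exposure is also documented by dose data on the CRF, tablet counts and pharmacy logs. No test in section 16 rests on diary BP, and the toxicity stopping guide uses treatment-related events of grade 3 or higher, collected until 30 days after the last dose.

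Most of this is right, and it limits the size of the point. The intervals above are gaps in scheduled readings, not delays in diagnosis; study-drug intake is well backed up; and the consequence is for safety data only. It does not remove the inconsistency. Section 8.2 a is firmer than encouragement: it says patients or carers will record BP daily and that the CRF should carry the average. Section 9.0 requires CRF entries to reflect source data, and after progression 8.3 leaves that average without a specified source. Reading the texts together simply means accepting the loss in patients still on drug.

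**Conclusion.** The concern holds. Section 8.3 applies a progression cut-off that fits dexamethasone to two items that should follow treatment. For patients treated past progression, the written home BP record and the daily study-drug record end while exposure continues. Scheduled clinic BP then falls 42 days apart (at most 48 within the windows), alongside 3-weekly adverse event review and the Table 7 checks for known hypertensives.

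This rests on sites following 8.3 literally and on the patient having no previously identified hypertension. The loss is at most one written reading per day, and the number of patients cannot be sized from the protocol. Progression-free survival, sample size and error rates are untouched. It is a worthwhile correction to safety data collection, not a threat to the trial's main conclusion.

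**What to change.** Amend section 8.3 so that BP and study-drug entries continue until all trial treatment is permanently discontinued, whether or not progression has been documented. Keep the progression cut-off for dexamethasone entries only, in line with section 8.2 h. This also removes the need to decide, for BP and drug intake, whether the first or the confirmatory scan counts as documented progression.

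The cost is one sentence, using the diary and home monitor already supplied. Patients treated beyond progression carry a modest extra diary burden. Patients who stop both drugs before progression would have less to record than under the current rule.

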## 8.4 Blood pressure monitors

Patients will be provided with a blood pressure monitor at the beginning of the trial (supplied to the site by either the Chief Investigator or the UCL CTC trial coordinator at site activation).

---

## 9.0 Data Management Guidelines

Data will be collected from sites on version controlled case report forms (CRFs) designed for the trial and supplied by UCL CTC. Data entered onto CRFs must reflect source data at site.

### 9.1 Completing Case Report Forms

All CRFs must be completed and signed by staff who are listed on the site staff delegation log and authorised by the PI to perform this duty. The PI is responsible for the accuracy of all data reported in the CRF.

Once completed the original CRFs must be sent to UCL CTC and a copy kept at site. All entries must be clear and legible. The use of abbreviations and acronyms must be avoided.

### 9.2 Corrections to CRFs

Any corrections made to a CRF at site must be made by drawing a single line through the incorrect item ensuring that the previous entry is not obscured. Each correction must be dated and initialled. Correction fluid must not be used. The amended CRF must be sent to UCL CTC and a copy retained at site.

### 9.3 Missing Data

To avoid the need for unnecessary data queries CRFs must be checked at site to ensure there are no blank fields before sending to UCL CTC. When data is unavailable because a measure has not been taken or test not performed, enter "ND" for not done. If an item was not required at the particular time the form relates to, enter "NA" for not applicable. When data are unknown enter the value "NK" (only use if every effort has been made to obtain the data).

### 9.4 Data Queries

Data arriving at UCL CTC will be checked for completeness, accuracy and consistency. Queries on incomplete, inaccurate or inconsistent data will be sent to the data contact at site. When responding to a query, site staff should attach an amended copy of the case report form held at site and send to

UCL CTC, keeping a copy at site. All amendments must be initialled and dated. All data which requires query will be queried at least once

## 9.5 Timelines for data return

Sites must complete and return CRFs to UCL CTC as soon as possible after patient visit and within one month of the patient being seen. The registration form should be faxed to the UCL CTC asap when completed to enable randomisation (see [section 6.0](#)). SAE reports should be sent via fax according to the timelines in [section 10.2.2](#) (SAEs).

Sites who persistently do not return data within the required timelines may be suspended from recruiting further patients into the trial by UCL CTC.

---

## 10.0 Pharmacovigilance

### 10.1 Definitions of Adverse Events

The following definitions have been adapted from Directive 2001/20/EC, ICH E2A "Clinical Safety Data Management: Definitions and Standards for Expedited Reporting" and ICH GCP E6:

#### Adverse Event (AE)

Any untoward medical occurrence or effect in a patient treated on a trial protocol, which does not necessarily have a causal relationship with a trial treatment. An AE can therefore be any unfavourable and unintended sign (including an abnormal laboratory finding), symptom or disease temporally associated with the use of a trial treatment, whether or not related to that trial treatment.

#### Adverse Reaction (AR)

All untoward and unintended responses to a trial treatment related to any dose administered. A causal relationship between a trial treatment and an adverse event is at least a reasonable possibility, i.e. the relationship cannot be ruled out.

#### Serious Adverse Event (SAE) or Serious Adverse Reaction

An adverse event or adverse reaction that at any dose:

- Results in death
- Is life threatening (the term "life-threatening" refers to an event in which the patient was at risk of death at the time of the event. It does not refer to an event that hypothetically might have caused death if it were more severe)
- Requires in-patient hospitalisation or prolongs existing hospitalisation
- Results in persistent or significant disability/incapacity
- Is a congenital anomaly or birth defect
- Is otherwise medically significant (e.g. important medical events that may not be immediately life-threatening or result in death or hospitalisation but may jeopardise the patient or may require intervention to prevent one of the other outcomes listed above)

#### Suspected Unexpected Serious Adverse Reaction (SUSAR)

A serious adverse reaction, the nature or severity of which **is not consistent** with the applicable trial treatment information.

## 10.2 Reporting Procedures

### 10.2.1 All Adverse Events (AEs)

All adverse events that occur between informed consent and 30 days post last trial treatment administration must be recorded in the patient notes and the trial CRFs. Information regarding dates of event onset and resolution, outcome, severity and causality for the trial treatment must be recorded. AEs thought to be caused by trial treatment will be followed up until resolution or death.

Those meeting the definition of a Serious Adverse Event (SAE) must also be reported to UCL CTC using the trial specific SAE Report (see [section 10.2.2](#) (Serious Adverse Events) for details).

Pre-existing conditions do not qualify as adverse events unless they worsen.

#### 10.2.1.1 Overdoses

All accidental or intentional overdoses, whether they result in an adverse event or not, must be recorded in the patient notes and CRFs. Overdoses resulting in an adverse event are classified as SAEs and must be reported to UCL CTC according to SAE reporting procedures. 'Other medically significant event' must be ticked as the classification of serious and the fact that an overdose has occurred must be clearly stated. See also [section 10.2.2](#) (Serious Adverse Events).

Sites must inform UCL CTC immediately when an overdose has been identified. See also [section 11.0](#) (Incident Reporting and Serious Breaches).

